This protocol outlines our plan to detect harmful DDIs more efficiently in routine care using high-throughput computing and automation. To do this, we will simultaneously conduct more than 200,000 population-based, new-user drug safety studies using 21 years of data from Ontario’s administrative health care databases (2002-2023). These databases contain encrypted data on all health care visits and hospitalizations of Ontario residents—all of whom have universal access to hospital care and physician services through a government-funded single-payer system, with Ontarians aged 65 years and older also receiving universal outpatient prescription drug coverage.

Following the application of inclusion and exclusion criteria, we will analyze a refined set of medication cohorts, each containing an exposed group (individuals prescribed a certain pair of medications) and a referent group (individuals prescribed a single medication). The exposed and referent groups will be statistically balanced on more than 400 baseline health characteristics. We will assess 74 clinically relevant outcomes and conduct extensive sensitivity and bias analyses to minimize false discoveries. Harmful DDIs that meet prespecified criteria will be further examined in additional and exploratory analyses. This study’s objective is to identify credible signals of harmful DDIs in older adults in routine care.

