#### Analysis to Balance the Exposed and Referent Groups in Each Cohort

Propensity scores will be calculated using multivariable logistic regression, incorporating more than 400 baseline characteristics (the complete list and coding definitions are provided in Multimedia Appendix 2). Characteristics include calendar year, prior use of drug A, demographics (eg, age, sex, neighborhood income quintile, urban vs rural residence, geographic region [31], and long-term care home residency), comorbidities (eg, asthma, diabetes, coronary artery disease) assessed over the 5 years before cohort entry, health care use in the year prior (eg, hospitalizations, emergency room visits, specialist consultations), and prescription drug dispensing within 120 days before cohort entry. The 120-day lookback period accounts for potential delays in prescription refills, ensuring comprehensive capture of medication dispensing.

The propensity scores will estimate the probability of a patient being in the exposed group versus the referent group, given their baseline characteristics. To enhance the comparability of the exposed and referent groups, we will exclude (1) individuals in the referent group with propensity scores lower than the lowest 1% of scores in the exposed group and (2) individuals in the exposed group with propensity scores higher than the highest 99% of scores in the referent group. This will also ensure that we do not violate the positivity assumption in causal inference, which requires that there should be a nonnull probability across each stratum of baseline characteristics within both the exposed and referent groups [32].

Inverse probability of treatment weighting (IPTW) using average treatment-effect-in-the-treated (ATT) weights will then be used to balance the exposed and referent groups on baseline characteristics as follows: Individuals in the referent group will be weighted using ATT weights, defined as their odds of being in the exposed group (propensity score/[1 − propensity score]). Individuals in the exposed group (the medication pair group) will receive weights of 1. This method will produce a weighted pseudosample of individuals in the referent group with a distribution of measured characteristics similar to that of the exposed group [33,34]. Between-group differences in baseline characteristics in the weighted samples will be examined using standardized differences (SDs) [35].

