Cohorts will be excluded from further analysis if fewer than 95% of the baseline characteristics are balanced between the exposed and referent groups (ie, the SDs must be <10% for ≥95% of the characteristics).

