#### Regression Analyses

A visual summary of the regression and additional exploratory analyses is provided in Multimedia Appendix 4. In each cohort, outcomes will be eligible for analysis if there are at least six outcome events in both the exposed and referent groups. Reporting fewer than six events could lead to potential patient reidentification and substantial estimation errors.

For each eligible cohort, we will use a modified Poisson regression model [36] to estimate the weighted risk ratio (RR) and its 95% CI for each outcome in the exposed group compared to the referent group. Additionally, a binomial regression model with an identity link function will be used to estimate the weighted risk difference (RD) and its 95% CI. If all 74 outcomes for a particular cohort are eligible, up to 74 regression models will be run.

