#### Criteria for Identifying Potential Signals of Harmful DDIs

Associations between a drug pair and an adverse outcome that meet the following criteria will be considered potential signals of harm and analyzed further:

Thresholds for RRs and RDs. The lower bound of the 95% CI for the RR must be ≥1.33, and for the RD, it must be ≥0.1%. These thresholds were chosen to ensure that only clinically significant increases in risk (of sufficient magnitude to be of concern) are considered. This analysis will focus solely on potential harms from drug combinations rather than protective benefits.Statistical significance. The *P* values from the modified Poisson regression model (for RRs) and the binomial regression model (for RDs) must be statistically significant after applying the Benjamini-Hochberg correction. This correction accounts for multiple comparisons across all outcomes and drug pair cohorts. The false discovery rate will be set at 5%, and the highest *P* value below the Benjamini-Hochberg critical value will be considered statistically significant, along with all *P* values below it. This correction will minimize the risk of false-positive discoveries (type I errors).

Drug pair cohorts that do not generate significant signals will not undergo further analysis.

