Survival analysis. To assess whether the initial signal persists when analyzed using a time-to-event approach, we will conduct a Cox proportional hazards regression with a 30-day follow-up period, censoring on death when all-cause mortality is not the outcome of interest. We will test the proportional hazards assumption by including an interaction term between the new-user status and follow-up time. This analysis will help determine whether the signal is robust across different modeling techniques.Negative-control exposure analyses. To detect potential biases from unobserved confounders, we will perform negative-control exposure analyses. A negative-control exposure is a variable that shares the same sources of bias as the drug of interest but cannot plausibly cause the outcome. We will rerun the regression analyses for the initial signals using a control exposure period starting 90 days before cohort entry [37]. This analysis will help identify any confounding factors that may have influenced the initial signal. Notably, the outcome of all-cause mortality cannot be examined with this method, as all patients lived to their cohort entry date. A positive association (ie, RRs and RDs significantly different from null, with *P*<.05) in this analysis would suggest potential confounding, whereas the absence of an association would bolster the credibility of the original signal.E-value analysis. We will conduct E-value analyses to quantify the minimum strength of association an unmeasured confounder would need to have with both the drug combination and the outcome to negate the observed signal [38]. Larger E-values indicate that substantial unmeasured confounding would be required to explain away the signal, whereas smaller E-values suggest that minimal unmeasured confounding could do so. For an initial signal to be considered robust, the E-value must exceed 2.Propensity score matching. To further validate the robustness of the signal, we will use 1:1 propensity score matching to balance the exposed and referent groups on baseline characteristics [39]. This method estimates the average treatment effect in the treated and mitigates the influence of extreme weights, which can occur with IPTW. Consistency between the results of this analysis and the initial findings will strengthen the validity of the signal.Bootstrap analysis. We will use a multiplier bootstrap procedure to compute RRs and RDs across 200 random samples, each of the same size as the original cohort. This method helps correct SEs and CIs, ensuring they have the correct coverage rates [36,40]. For the signal to be considered robust, at least 90% of the bootstrap samples must yield results consistent with the original findings, with *P*<.05 and CIs for RRs and RDs in the same direction as initially observed.

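### The 95% balance rule sets no ceiling on the other 5% of more than 400 characteristics, and the only later re-balancing, matching, has no stated balance or pass rule

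*Protocol article*

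**What the plan says.** In the Protocol article, section Analysis to Balance the Exposed and Referent Groups in Each Cohort, the propensity model is described as "incorporating more than 400 baseline characteristics". After trimming and weighting, the retention rule is: "Cohorts will be excluded from further analysis if fewer than 95% of the baseline characteristics are balanced", explained as "the SDs must be <10% for ≥95% of the characteristics". The Introduction describes the result as groups that "will be statistically balanced on more than 400 baseline health characteristics".

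Under Regression Analyses, the modified Poisson model is used "to estimate the weighted risk ratio (RR) and its 95% CI for each outcome in the exposed group compared to the referent group", and a binomial model with identity link gives the RD. No covariates are named for either model.

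Under Criteria for Identifying Potential Signals of Harmful DDIs, the requirement is: "The lower bound of the 95% CI for the RR must be ≥1.33, and for the RD, it must be ≥0.1" (the last figure in per cent), plus significance after the Benjamini-Hochberg correction.

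Under Sensitivity and Bias Analyses to Guard Against Spurious Discoveries, signals go through Cox regression, a negative-control exposure period, an E-value criterion (above 2), matching and a bootstrap. On matching: "we will use 1:1 propensity score matching to balance the exposed and referent groups on baseline characteristics". Its result is read as follows: "Consistency between the results of this analysis and the initial findings will strengthen the validity of the signal".

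**The concern.** The rule counts every characteristic equally and says nothing about those that fail. Low-prevalence items pass easily: 1% versus 2%, a doubling, is a standardized difference of only about 8%. The list includes many comorbidities and dispensed drugs, where low prevalence is plausible. The quota can then be filled largely by uninformative items while age, recent hospital use or the indication for drug B is among those that miss the limit.

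If that happens and the outcome model contains only exposure, a known and measured imbalance goes straight into the RR and RD. The Benjamini-Hochberg correction does not protect against this, because it controls chance findings and not bias. At stake is the credibility of individual signals, which would be reported as coming from groups balanced on more than 400 characteristics.

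**Working it through.** The plan states no count of tolerated imbalances and no bias estimate, so there is no figure of its own to reproduce.

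**Inputs from the article:** more than 400 characteristics (400 taken as the floor); standardized difference below 10% for at least 95% of them; RR lower 95% bound of at least 1.33; E-value above 2. **Assumed, not in the article:** covariate prevalences, covariate-outcome risk ratios and event counts.

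**1. Tolerated number.** n − ceil(0.95n): 20 of 400, 21 of 420, 25 of 500.

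**2. Easy passes.** For a binary covariate, SD = (p1 − p0)/√{[p1(1−p1) + p0(1−p0)]/2}. For 2% versus 1%: 0.01/√[(0.0196 + 0.0099)/2] = 0.01/0.1214 = 0.082.

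**3. Bias from one covariate.** Bias = [1 + p1(RRc − 1)]/[1 + p0(RRc − 1)], where RRc is the covariate's risk ratio for the outcome. For 45% versus 30%, SD = 0.15/√[(0.2475 + 0.21)/2] = 0.31. With RRc 2.5, bias = (1 + 0.45×1.5)/(1 + 0.30×1.5) = 1.675/1.45 = 1.155.

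**4. Several such covariates,** independent and in the same direction: 1.155² = 1.33, 1.155³ = 1.54, 1.155⁴ = 1.78, 1.155⁵ = 2.06.

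**5. Point RR needed under a true RR of 1.** The lower bound must be at least 1.33. With e events per group and SE(log RR) ≈ √(2/e), ignoring the effect of weighting on the variance, the point RR must be 1.33 × exp(1.96√(2/e)):
- 2000 events: 1.42, reached with three covariates (1.54)
- 500 events: 1.51, reached with three (1.54)
- 100 events: 1.75, reached with four (1.78)
- 50 events: 1.97, reached with five (2.06)

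At exactly the needed point RR, about half of such cohorts would pass. The RD threshold and the Benjamini-Hochberg step must be met as well and are not modelled here, so these counts are minimums.

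**6. Other assumptions** (referent prevalence 10%). One covariate alone gives a bias of 1.33 only if RRc is about 10.5 at SD 0.2, 5.5 at SD 0.3 or 3.1 at SD 0.5. At the 10% limit itself, one covariate gives only 1.05 (RRc 3) or 1.09 (RRc 5). Twenty covariates in the same direction give:
- SD 0.1: 1.13 (RRc 1.2) or 1.35 (RRc 1.5)
- SD 0.2: 1.30 (RRc 1.2) or 1.89 (RRc 1.5)

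So the result runs from no signal to a clear one, depending on assumptions that the article cannot settle.

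**7. E-value criterion.** E = RR + √[RR(RR − 1)]. At RR = 4/3, E = 4/3 + √(4/9) = 2 exactly; at 1.33, E = 1.99. A signal whose lower bound is already at least 1.33 almost always meets it, whether E is computed from the estimate or from the bound.

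**8. Other later steps.** Cox regression and the bootstrap are not described as re-balancing, so on the same comparison they would reproduce its bias. The negative-control period can reveal persistent confounding but does not correct the estimate, is unavailable for mortality, and may miss an acute indication that was absent 90 days earlier. Matching does re-balance. However, the bootstrap has a stated pass rule (at least 90% of samples) and the E-value has one (above 2), whereas matching has neither a pass rule nor a standardized-difference check.

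**The case against.** The strongest reply is that the plan does not stop at the 95% rule. Every signal is matched 1:1 on baseline characteristics and, except for mortality, rerun in a control period. Step 1 of the overall framework makes support from the sensitivity and bias analyses part of identifying a signal. A reader might infer from the retention rule that nothing downstream deals with the residual imbalance. The article does not support that, because matching is a second attempt at balancing the same measured variables. What remains is that its success is not tied to any stated balance check or numeric rule.

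A second tempting inference is that two covariates of the size above are enough, since their joint bias is 1.33. They are not, because 1.33 applies to the lower confidence bound. At the reported median of 583 new users per initial cohort and an assumed 5% risk, there are about 29 exposed events. Even with a very large referent group the point RR must be about 1.33 × exp(1.96/√29) = 1.9, which takes five such covariates.

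The scenario also needs imbalances around 31% that survive weighting, point the same way and act independently. Hospital use, age and comorbidity are themselves in the propensity model, and nothing in the article shows that strong predictors would concentrate in the failing 5%. Correlated covariates would add less than their product. These points stand and limit the size of the concern.

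Finally, the article is condensed and its appendices are not shown, so covariate adjustment or a matched-balance check may be specified elsewhere. But the retention rule is stated in full as an operating rule, and it has no ceiling. The output is also a screening signal that still goes to pharmacological and epidemiological review, which lowers the stakes without removing the bias.

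**Conclusion.** The concern holds in a limited form. The retention rule allows 20 or more characteristics to remain at a standardized difference of 10% or above, without a maximum and without protecting strong outcome predictors, and the primary models are not described as adjusting for them. The later steps do not reliably close this gap, for the reasons in items 7 and 8 of the working.

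For a pair with no true effect, a false signal needs a biased point RR of roughly 1.4 to 1.75 or more, depending on events. Under the assumed 45% versus 30%, outcome RR 2.5, independence and common direction, that is about three to five covariates, well inside the number permitted. Under milder assumptions no signal arises. The article does not show that such imbalances will occur, only that the rule as written would let them through. This calls for an inexpensive improvement and does not invalidate the design.

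**What to change.** Keep the 95% rule and add two steps for flagged signals only.

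1. Refit the weighted RR and RD models including every covariate whose standardized difference is still 10% or above. Retain the signal only if both lower bounds still meet their thresholds. Where events are few, use a penalised fit or a further re-weighting step.
2. Apply the same standardized-difference check to the matched sample, and state what result counts as consistent with the primary analysis.

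Optionally, require a standardized difference below 10% for a short prespecified core set, such as age, sex, calendar year, long-term care residence, prior-year hospital and emergency use, and prior history of the outcome.

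The cost is one extra refit and one balance table per flagged signal. Some signals will be lost, and refits will be imprecise where events are few. The identity-link binomial model may also fail to converge with added covariates, so a fallback should be named. The optional core-set rule would also exclude some cohorts.

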#### Regression Analyses

A visual summary of the regression and additional exploratory analyses is provided in Multimedia Appendix 4. In each cohort, outcomes will be eligible for analysis if there are at least six outcome events in both the exposed and referent groups. Reporting fewer than six events could lead to potential patient reidentification and substantial estimation errors.

For each eligible cohort, we will use a modified Poisson regression model [36] to estimate the weighted risk ratio (RR) and its 95% CI for each outcome in the exposed group compared to the referent group. Additionally, a binomial regression model with an identity link function will be used to estimate the weighted risk difference (RD) and its 95% CI. If all 74 outcomes for a particular cohort are eligible, up to 74 regression models will be run.

#### Criteria for Identifying Potential Signals of Harmful DDIs

Associations between a drug pair and an adverse outcome that meet the following criteria will be considered potential signals of harm and analyzed further:

Thresholds for RRs and RDs. The lower bound of the 95% CI for the RR must be ≥1.33, and for the RD, it must be ≥0.1%. These thresholds were chosen to ensure that only clinically significant increases in risk (of sufficient magnitude to be of concern) are considered. This analysis will focus solely on potential harms from drug combinations rather than protective benefits.Statistical significance. The *P* values from the modified Poisson regression model (for RRs) and the binomial regression model (for RDs) must be statistically significant after applying the Benjamini-Hochberg correction. This correction accounts for multiple comparisons across all outcomes and drug pair cohorts. The false discovery rate will be set at 5%, and the highest *P* value below the Benjamini-Hochberg critical value will be considered statistically significant, along with all *P* values below it. This correction will minimize the risk of false-positive discoveries (type I errors).

Drug pair cohorts that do not generate significant signals will not undergo further analysis.

#### Sensitivity and Bias Analyses to Guard Against Spurious Discoveries

Signals of potentially harmful DDIs will undergo the following sensitivity and bias analyses to ensure that identified signals are not artifacts of statistical or methodological bias but are credible associations worthy of further investigation:

Survival analysis. To assess whether the initial signal persists when analyzed using a time-to-event approach, we will conduct a Cox proportional hazards regression with a 30-day follow-up period, censoring on death when all-cause mortality is not the outcome of interest. We will test the proportional hazards assumption by including an interaction term between the new-user status and follow-up time. This analysis will help determine whether the signal is robust across different modeling techniques.Negative-control exposure analyses. To detect potential biases from unobserved confounders, we will perform negative-control exposure analyses. A negative-control exposure is a variable that shares the same sources of bias as the drug of interest but cannot plausibly cause the outcome. We will rerun the regression analyses for the initial signals using a control exposure period starting 90 days before cohort entry [37]. This analysis will help identify any confounding factors that may have influenced the initial signal. Notably, the outcome of all-cause mortality cannot be examined with this method, as all patients lived to their cohort entry date. A positive association (ie, RRs and RDs significantly different from null, with *P*<.05) in this analysis would suggest potential confounding, whereas the absence of an association would bolster the credibility of the original signal.E-value analysis. We will conduct E-value analyses to quantify the minimum strength of association an unmeasured confounder would need to have with both the drug combination and the outcome to negate the observed signal [38]. Larger E-values indicate that substantial unmeasured confounding would be required to explain away the signal, whereas smaller E-values suggest that minimal unmeasured confounding could do so. For an initial signal to be considered robust, the E-value must exceed 2.Propensity score matching. To further validate the robustness of the signal, we will use 1:1 propensity score matching to balance the exposed and referent groups on baseline characteristics [39]. This method estimates the average treatment effect in the treated and mitigates the influence of extreme weights, which can occur with IPTW. Consistency between the results of this analysis and the initial findings will strengthen the validity of the signal.Bootstrap analysis. We will use a multiplier bootstrap procedure to compute RRs and RDs across 200 random samples, each of the same size as the original cohort. This method helps correct SEs and CIs, ensuring they have the correct coverage rates [36,40]. For the signal to be considered robust, at least 90% of the bootstrap samples must yield results consistent with the original findings, with *P*<.05 and CIs for RRs and RDs in the same direction as initially observed.

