#### Cohort Entry Dates for Exposed and Referent Groups

The exposed group will comprise regular users of drug A and new users of drug B, as described earlier. The cohort entry date for individuals in the exposed group will be the start date of drug B. The referent group will comprise regular users of drug A who are not coprescribed drug B. The cohort entry date for individuals in the referent group will be assigned based on the distribution of the time differences between the most recent prescription for drug A and the initiation of drug B for individuals in the exposed group, ensuring similar observation periods between groups [25].

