High-throughput computing and automated analytical pipelines have proven effective for detecting potential DDIs in large health care datasets in other countries, such as the United States. Previous studies by Bykov et al [14] and Leonard et al [15] have demonstrated that these methods can efficiently confirm known interactions and identify novel signals. However, these approaches have largely been limited to single-object drugs, specific outcomes, or nonrepresentative datasets (derived from a specific subset of the population, such as those with a certain type of insurance, rather than the entire population), which may restrict generalizability. Building on these advances, our study will use high-throughput computing to analyze Ontario’s population-based, linked administrative databases, which capture comprehensive prescription and outcome data across the province’s universal health care system. Using a population-based, new-user cohort design, we will systematically evaluate nearly 200,000 medication pairs among 3.8 million older adults—an effort that would be impractical with traditional methods. This approach will not only fill a critical gap by providing large-scale, real-world evidence in a Canadian context but also enhance generalizability, generate signals that could inform clinical decision-making once validated, and strengthen postmarketing pharmacovigilance efforts for older adults. To the best of our knowledge, this represents the first application of such an approach in Canada, leveraging the strengths of a universal health care setting to further enhance the generalizability and clinical relevance of detected DDI signals.

The cohort study is designed to mimic typical clinical scenarios, for example, an individual who has been taking digoxin for 7 months and is then newly prescribed sulfamethoxazole-trimethoprim to treat a urinary tract infection. In DDI studies, such scenarios are categorized as follows:

Precipitant triggered: Individuals initiate the object drug first, followed by the precipitant, with follow-up starting on the day the precipitant is initiated.Object triggered: Individuals initiate the precipitant first, followed by the object drug, with follow-up starting on the day the object is initiated.

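### The control period starting 90 days before cohort entry can reveal only confounding already present then, so a null result should not count as support against confounding by a new acute illness for which drug B was started

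*Protocol article*

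**What the plan says.** All of this is in the protocol article.

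- **Purpose.** Under *Sensitivity and Bias Analyses to Guard Against Spurious Discoveries*: "To detect potential biases from unobserved confounders, we will perform negative-control exposure analyses".
- **Validity condition.** Same section: "A negative-control exposure is a variable that shares the same sources of bias as the drug of interest but cannot plausibly cause the outcome".
- **Implementation.** Same section: "We will rerun the regression analyses for the initial signals using a control exposure period starting 90 days before cohort entry". The article does not give the end of this period. A rerun of the 30-day analysis would suggest roughly days -90 to -60.
- **Reading of the result.** A positive association ("RRs and RDs significantly different from null, with *P*<.05") is taken to suggest confounding, "whereas the absence of an association would bolster the credibility of the original signal". Nothing limits this to confounders that are stable over time. All-cause mortality is exempt, because everyone was alive at entry.
- **Time zero and comparator.** Under *Cohort Entry Dates for Exposed and Referent Groups*: "The cohort entry date for individuals in the exposed group will be the start date of drug B", and "The referent group will comprise regular users of drug A who are not coprescribed drug B".
- **Typical use.** The Discussion (*Summary*) pictures a long-term digoxin user who is "newly prescribed sulfamethoxazole-trimethoprim to treat a urinary tract infection".
- **Role in the decision.** Step 1 of the *Overall Framework* section requires a signal to be supported in the sensitivity and bias analyses.

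**The concern.** A control period is useful only for a bias that operates in it. Cohort entry for the exposed is the day B is dispensed, so when B treats an acute illness, that illness arises at or shortly before day 0. Referents are users of A without B, and nothing makes them share the illness. Three months earlier a new infection is no commoner in future B starters than in referents. For this confounder the control lacks the property that the article itself requires.

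The use case is not marginal. The *Results* section describes cohorts with amoxicillin added to levothyroxine (197,057 patients) and ciprofloxacin added to amoxicillin (4220 patients). The outcome list includes sepsis, pneumonia, chest X-ray, delirium, and urinary tract infection or urine culture, any of which may be a manifestation or work-up of the treated illness. For such pairs an association produced by the illness would tend to give a null control result, and the article would count that null in the signal's favour.

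**Working it through.** The article gives no power or error rate for this check, so there is no figure to reproduce. The check is reasoning plus an illustration.

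**Inputs from the article.** 583 new users per cohort (median) and 2130 (upper quartile), from *Results*. Signal thresholds: lower 95% limits of at least 1.33 for the RR and 0.1% for the RD. At least six events per group. Control flagged at P<.05 on both RR and RD.

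**Assumptions, not in the article.** No drug effect. Four referents per exposed person. 30-day risk 4% if ill and 1.5% if not. Illness at entry in 2% of referents and in 80%, 60% or 40% of B starters. Illness in 2% of both groups at day -90. Unweighted binomial counts, 200,000 replicates, before Benjamini-Hochberg.

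**Step 1: risks in the main analysis.**
- Referent: 0.02 × 4% + 0.98 × 1.5% = 1.55%.
- Exposed, 80% ill: 0.8 × 4% + 0.2 × 1.5% = 3.5%, RR 3.5/1.55 = 2.26.
- Exposed, 60% ill: 3.0%, RR 1.94.
- Exposed, 40% ill: 2.5%, RR 1.61.

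**Step 2: how often the false association meets the thresholds, and how often the control flags it.** The control compares 1.55% with 1.55%.

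| Ill among B starters | 583 exposed / 2332 referents | 2130 / 8520 |
|---|---|---|
| 80% | 48% | 95% |
| 60% | 26% | 69% |
| 40% | 10% | 23% |
| Control flags, harmful direction | 1.2% | about 1.7% |
| Control flags, either direction | 1.2% | about 3.8% |

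With 80% ill but a risk of 3% rather than 4% if ill, the threshold rates are 16% and 44%.

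**Step 3: does the end of the control period matter?** Let a share q of B starters and 2% of referents be ill, and let illness multiply the risk by m. Main RR = (1 + q(m-1)) / (1 + 0.02(m-1)). With q = 0.5 and m = 5 this is 3/1.08 = 2.78. Over days -90 to -60 the control RR is 1.00. If the period runs to day 0 and the illness begins 3 days before entry, the control RR is (87 + 3 × 3)/(87 + 3 × 1.08) = 96/90.24 = 1.06. Over four settings (q from 0.3 to 0.9, m of 5 or 10) the main RR runs from 2.04 to 7.71 and this long-window control RR from 1.04 to 1.26. The longer window dilutes the illness rather than missing it altogether.

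**Step 4: what the check can see.** If a fraction f of the illness excess already exists at day -90 (q = 0.5, m = 5), the control RR is (1 + 4(0.02 + 0.48f))/1.08. That gives 1.18 for f = 10%, 1.44 for 25%, 1.89 for 50% and 2.78 for 100%. Stable or recurrent confounding does show.

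**Step 5: do the other Step 1 checks cover the gap?** Cox regression, 1:1 matching and the bootstrap reuse the same groups and measured covariates. The E-value must exceed 2. At RR 1.33 it is 1.33 + √(1.33 × 0.33) = 1.99, and it passes 2 at RR 1.334, so it removes almost nothing that the 1.33 threshold has not already removed. None targets the reason for starting B.

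**The case against.** Several points on the other side stand and limit the finding.

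- **A null result only adds weight.** A reader might infer that confounded signals are passed as established. The document does not support that. The section aims at associations worth investigating further, and the framework then requires pharmacological, interaction-checker and epidemiological review by two reviewers. The limitations section admits residual confounding, and the bidirectional comparison is aimed partly at it. However, that comparison only highlights concordant pairs and is meant mainly for chronic drugs, and literature review does not correct a biased estimate.
- **A reader might infer that the check can never detect acute illness.** That is exact only if the illness is new and the period closes before entry. The article does not say where the period ends, and recurrent or prodromal illness could show (Steps 3 and 4).
- **Death.** It is tempting to list death among the affected outcomes. The article exempts all-cause mortality from this check, so no misleading null arises there.
- **Size.** The near-zero flag rate follows from assuming equal illness at day -90. The threshold rates depend strongly on the illness share and precede multiplicity correction. The 48% and 95% are the top of the range, not typical values.

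What the objection does not remove is the mismatch inside one section: the control must share the sources of bias, the chosen period does not share this one, and a null is read without restriction.

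**Conclusion.** The concern holds in a limited form. The control period informs only about confounding present in it. Where B is started for a new acute illness, the control does not meet the article's own definition, and a null result is not evidence against confounding by that illness. Nor should it count as Step 1 support on that question.

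Under the stated assumptions, illness alone produces a false association meeting the thresholds in about 10% to 48% of cohorts with 583 exposed and 23% to 95% with 2130, before Benjamini-Hochberg. The control flags at most about the nominal alpha. The illness prevalences, risks and referent ratio are not in the document, so these figures show the mechanism and a plausible range; they do not forecast the study's false-signal rate. The check remains sound for stable and recurrent confounding, and all-cause mortality is outside this point.

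**What to change.** Keep the check and change what is concluded from it:

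1. State that a null result speaks only to confounding present in the control period, and state where that period ends.
2. For signals where B treats an acute condition, do not count the null as Step 1 support. Label such signals *confounding by acute indication not excluded*.
3. Where a suitable drug for the same acute indication exists, add a supplementary comparison of starters of B with starters of that drug among regular users of A. It should supplement the control period, not replace it, and carry no mandatory RR threshold. Replacement would discard a check that works for stable confounding. A threshold would turn a different estimand into a gate, so that a true harm could fail if the comparator also interacts with A.

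**Cost.** Items 1 and 2 are wording plus a classification of drug B as acute or not. Some acute-B signals will carry a weaker credibility label. Item 3 needs the indication to be inferred from claims, since the drug database is described only as prescription claims. It also needs a comparator mapped for each B, and some groups will be small.
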